#### Blinding

2.2.7

Patients, outcome assessors, and statisticians will turn a blind eye to this assignment. However, due to the characteristics of acupuncture, acupuncturists will not be deceived in this trial. Patients will not know their group status and patients in different treatment groups will be treated in different treatment rooms. Besides, they will be separated by a curtain to avoid communication during the trial. For the successful implementation of blinding, all researchers will be trained before the start of the trial.

### Intervention

2.3

All patients will receive treatment for 8 weeks, twice a week (every Monday and Thursday), 30 minutes each time, a total of 16 sessions. Acupuncturists will be required to hold a Chinese medicine practitioner license and have more than 1 year of clinical experience. The treatment will use sterile disposable steel needles (Jiajian brand in Wuxi, Jiangsu, China: Suxie Zhuzhun 20152200225). According to the different acupuncture points and the depth of acupuncture, sterile disposable steel needles of different specifications will be selected. And acupuncture will be artificially stimulated for 10 seconds to achieve “Deqi”. That is, the subject will have special sensations such as soreness, numbness, swelling, and weight. And the surgeon has feelings of tightness under the needle.

#### Group A

2.3.1

Group A will receive SSGA. The acupuncturist will use sterile disposable steel needles to stimulate left SP9 (Yinlingquan), left SP8 (Diji), left SP7 (Lougu), right ST36 (Zusanli), right ST37 (Shangjuxu), right ST39 (Xiajuxu). After routine disinfection, the acupuncturist will insert disposable steel needles vertically into SP9, SP8, SP7, ST36, ST37, and ST39. The specific selection of acupuncture points, needle specifications and the depth of acupuncture are shown in Table 1 and Figure 2 below.

**Table 1 T1:** Locations for group A.

Acupoint	Location	Needle specifications	Depth of acupuncture
SP9 (Yinlingquan)	Medial condyle of the tibia and the medial border of the tibia	0.25 × 50 mm	25–40 mm
SP8 (Diji)	3 cun directly below SP9, posterior border of medial margin of tibia	0.25 × 50 mm	25–40 mm
SP7 (Lougu)	6 cun above the tip of the medial malleolus, posterior margin of the medial edge of the tibia	0.25 × 50 mm	25–40 mm
ST36 (Zusanli)	3 cun directly below ST35, and one finger-breadth lateral to the anterior border of the tibia	0.25 × 50 mm	25–40 mm
ST37 (Shangjuxu)	6 cun directly below ST35, and one finger-breadth lateral to the anterior border of the tibia	0.25 × 50 mm	25–40 mm
ST39 (Xiajuxu)	9 cun directly below ST35, and one finger-breadth lateral to the anterior border of the tibia	0.25 × 50 mm	25–40 mm

^a^1 cun (≈ 20 mm) is defined as the width of the interphalangeal joint of the patient's thumb.

**Figure 2 F2:**
[figure not shown]
Locations of acupoints in the trial. The acupoints include SP9 Yinlingquan, SP8 Diji, SP7 Lougu, ST36 Zusanli, ST37 Shangjuxu, ST39 Xiajuxu, LI11 Quchi, LI4 Hegu, ST44 Neiting, GB14 Yangbai.

#### Group B

2.3.2

Group B will receive conventional acupuncture treatment. The acupuncturist will use sterile disposable steel needles to stimulate, bilateral LI11 (Quchi), bilateral LI4 (Hegu), bilateral ST44 (Neiting), bilateral GB14 (Yangbai), bilateral SP9 (Yinlingquan), bilateral ST36 (Zusanli). The acupuncturist will insert the disposable steel needles vertically into LI11, LI4, ST44, GB14, SP9, and ST36 after routine disinfection. The specific selection of acupuncture points, needle specifications, and the depth of acupuncture are shown in Table 2 and Figure 2 below.

**Table 2 T2:** Locations for group B.

Acupoint	Location	Needle specifications	Depth of acupuncture
LI11 (Quchi)	The midpoint of the line between LU5 and lateral epicondyle of humerus	0.25 × 40 mm	20–30 mm
LI4 (Hegu)	Radial midpoint of the second metacarpal	0.25 × 25 mm	10–20 mm
ST44 (Neiting)	Between the second and third toes, the red and white flesh behind the webbed margin of the toe	0.25 × 25 mm	10–20 mm
GB14 (Yangbai)	1 cun on the eyebrow, pupils straight up	0.25 × 25 mm	7–15 mm
SP9 (Yinlingquan)	Medial condyle of the tibia and the medial border of the tibia	0.25 × 40 mm	20–30 mm
ST36 (Zusanli)	3 cun directly below ST35, and one finger-breadth lateral to the anterior border of the tibia	0.25 × 40 mm	20–30 mm

^a^1 cun (≈ 20 mm) is defined as the width of the interphalangeal joint of the patient's thumb.

### Outcome measures

2.4

#### Primary outcome

2.4.1

The primary outcome measurement will be expressed by the change in IGA score from baseline to the end of 8-week treatment. The IGA score is an overall assessment of the degree of inflammatory and non-inflammatory lesions and is divided into 6 levels.^[21,22]^

Grade 0 (0 points): the skin is smooth and clean, without any inflammatory or non-inflammatory lesions; Grade 1 (1 point): the skin is almost smooth, non-inflammatory lesions are rare, and no more than 1 small inflammatory lesion; Grade 2 (2 points): mild, with some non-inflammatory lesions, and only a few inflammatory lesions (only papules or pustules, no nodular lesions); Grade 3 (3 points): moderate, there are multiple non-inflammatory lesions, and there may be some inflammatory lesions, but no more than 1 small nodular lesion; Grade 4 (4 points): severe, with multiple non-inflammatory and inflammatory lesions, but only a few nodular lesions; Grade 5 (5 points): extremely severe, with multiple non-inflammatory and inflammatory lesions, and multiple nodular cystic lesions.

#### Secondary outcome measurements

2.4.2

The secondary measurements will be measured by changes in IGA, total facial lesion counts (Total Lesion Counts),^[21,23]^ inflammatory lesion counts, non-inflammatory lesion counts,^[21]^ and Acne-Specific Quality of Life^[24]^ at 8 and 12 weeks compared with baseline display.

Total lesion count includes inflammatory lesion counts and non-inflammatory lesion counts. Inflammatory lesions include inflammatory papules, pustules, cysts, and nodules. Non-inflammatory lesions include blackheads and whiteheads. Lesions will be evaluated on the forehead, cheeks, nose, and chin.

Acne-specific quality of life has 14 items in total, covering 3 areas, including self-perception, social function, and emotional function.^[24]^ This scale is mainly used to test the quality of life of patients with skin diseases. Each item is divided into 4 levels according to the specific conditions of the patient, with a score of 0 to 3. The total score of 16 items is the patient's skin disease quality of life score. The total index score is 30 points. The higher the score, the worse the patient's quality of life.

The Expectation and Credibility of treatment rating scale will be used to measure the patients’ attitudes to acupuncture after the first treatment. The patients will be asked the following question: “Do you think SSGA will be effective in treating the symptoms of ance?”

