#### Recruitment

2.2.5

Seventy six patients will be recruited through hospital outpatient clinics, advertisements on the hospital's social media (WeChat), and leaflets displayed by community service centers. The recruitment will provide a phone number so that potential patients can contact the researchers. The dermatologist will screen patients who meet the inclusion and exclusion criteria and use a digital camera (Canon EOS 200D) to take facial photos. The study assistant will be responsible for providing study information, such as the objectives, interventions, duration, benefits, and risks. Agreed to participate in the study patients will sign informed consent. The confidentiality of information recorded by patients will be protected.

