#### Clinical data analysis

2.5.1

Statistical analysis of all data will use IBM SPSS statistical version 24.0 software (IBM Corporation, Armonk, New York). For continuous variables, the data will be represented by the mean (standard deviation) or median (interquartile range) according to the normal distribution. Enumerated data will be displayed in percentage. For the primary outcome, we will calculate the IGA score at 8 weeks, and use the χ^2^ test to compare group A and group B. For secondary outcomes, continuous variables including IGA, TCL, Inflammatory lesion count, Non-inflammatory lesion count, Qol-Acne, and the Expectation and Credibility of acupuncture treatment will be compared at 8 and 12 weeks, using an unpaired Student *t* test or Wilcoxon rank-sum test (depending on the situation). A *P* value of <.05 will be considered a limit of statistical significance.

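### The expectation and credibility item asks both arms about SSGA, which Group B does not receive, and its analysis times do not match when it is measured

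*Protocol article*

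**What the plan says.** Section 2.4.2 (Secondary outcome measurements) introduces an expectation and credibility rating scale meant to capture patients' "attitudes to acupuncture after the first treatment". It continues, "The patients will be asked the following question", and gives a single item: "Do you think SSGA will be effective in treating the symptoms of ance". The item is not restricted to one arm, and no other wording is offered for the second arm.

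The arms are defined in sections 2.3.1 and 2.3.2: "Group A will receive SSGA" and "Group B will receive conventional acupuncture treatment". Section 2.2.7 (Blinding) states "Patients will not know their group status".

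Section 2.5.1 (Clinical data analysis) lists the scale with the other secondary outcomes and says that "the Expectation and Credibility of acupuncture treatment will be compared at 8 and 12 weeks", using an unpaired t test or a rank-sum test. The Methods paragraph of the Abstract agrees with 2.4.2 that the scale is given after the first session, and the legend of Figure 3 defines an abbreviation for that time point.

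**The concern.** A credibility scale in a two-arm trial of real acupuncture has one main use: to show whether patients in both arms found the treatment they were given equally convincing. If they did, a difference in a patient-reported outcome such as acne-specific quality of life is harder to attribute to expectation. This works only if each patient rates the treatment received. An item that names the experimental method does this for Group A and not for Group B.

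Two further matters follow. Patients are meant to be unaware of their group, and naming one arm's treatment in a questionnaire sits awkwardly with that. And the analysis section schedules comparisons at times for which no measurement is stated. The scale is given once, early in treatment, so answers to a badly worded item cannot be collected again later.

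**Working it through.** No figure in the plan depends on this item, so the check is a comparison of the text.

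**1. What each arm is asked, and what it receives**

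| | Group A | Group B |
|---|---|---|
| Treatment (2.3.1, 2.3.2) | SSGA | Conventional acupuncture |
| Treatment named in the item (2.4.2) | SSGA | SSGA |
| Treatment rated, taken literally | Own | Not own |
| Stated construct (2.4.2) | Attitude to acupuncture | Attitude to acupuncture |

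Section 2.5.1 uses an unpaired two-group test, so Group B has to answer the item. It cannot be read as a question for Group A alone.

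**2. What the comparison would estimate**

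Let *a* be Group A's mean rating of SSGA, *s* Group B's mean rating of SSGA, and *c* Group B's mean rating of the conventional acupuncture it receives.

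- Comparison wanted: *a* − *c*.
- Comparison obtained: *a* − *s*.
- Error: (*a* − *s*) − (*a* − *c*) = *c* − *s*.

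The error is zero only if Group B rates SSGA exactly as it rates its own treatment. The item never collects *c*, so neither the sign nor the size of the error can be estimated from trial data. Equal scores would not establish equal credibility, and unequal scores could not be interpreted.

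**3. Match to the construct**

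Section 2.4.2 says that the scale measures attitudes to acupuncture. The item asks about one named acupuncture method. It therefore matches neither the stated construct (acupuncture in general) nor the usual target (the treatment received) in Group B.

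**4. Timing**

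| Source | Time of the scale |
|---|---|
| Abstract, Methods | After session 1 |
| 2.4.2 | After session 1 |
| 2.5.1 | Compared at weeks 8 and 12 |

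The text states one measurement and two comparisons, and neither comparison falls at the time of the measurement.

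**5. Blinding**

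The same item is put to both arms, so the item alone carries no information about allocation. It could help a patient infer the group only if the patient also knew which points make up SSGA. The arms do look different: SSGA uses six one-sided points on the lower limbs (2.3.1), while Group B has bilateral points that include the forehead, elbow and hand (2.3.2). Section 2.2.5 says "The study assistant will be responsible for providing study information, such as the objectives, interventions, duration, benefits, and risks", but not whether the method's name or its points are disclosed. A patient told both could match name to needles. The documents do not say that this happens.

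**6. Reach**

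The item is put to 76 patients. Its content is wrong for Group B, about 76 / 2 = 38 patients at 1:1 allocation. It comes after session 1, with 16 − 1 = 15 sessions still to come. It enters neither the primary outcome (change in IGA to week 8, with assessors planned to be blinded) nor the sample size calculation.

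**The case against.** A reader might infer that the item undermines blinding in both arms: that Group A learns its treatment is the one under test and Group B learns that it has something else. The documents do not support this. An identical question cannot by itself separate the arms, and no section says that patients are told which points belong to SSGA. If patients simply assume that SSGA is what they received, allocation stays masked. Patients also hear about objectives and interventions before consent, so the name may already be known and the item may disclose nothing new. What remains is a possible risk to blinding, and through it to the patient-reported quality-of-life score, with no direction or size that can be derived.

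That same assumption offers a partial defence of the measurement. If every Group B patient took SSGA to mean their own treatment, *s* would equal *c* and the comparison would work. But the plan does not say that Group B will be led to believe this, and a valid comparison should not depend on patients misreading the question.

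On timing, the weeks in 2.5.1 close a sentence listing six outcomes, so loose drafting is a plausible explanation. The schedule in Figure 3 is not available here, so it cannot be excluded that later measurements appear there. The two sections still disagree as written.

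Finally, the article shows one item of a rating scale whose full form is not visible. That limits the point to this item; there is no basis for saying that other patient questionnaires name SSGA. It does not rescue the item, which is stated in full and is worded for one arm only.

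**Conclusion.** The point holds as a wording error in a secondary measure, together with an inconsistent analysis time. As written, Group A rates its own treatment and Group B rates one it does not receive. The between-group comparison in 2.5.1 then cannot show whether the treatments were equally credible, and the item misses its stated construct. Separately, the scale is measured after the first session but compared at weeks 8 and 12. Both conclusions follow from the text and need only the assumption that the item is used as printed. The misspelling in the item is immaterial.

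The risk to blinding is possible but not demonstrated; it depends on how much patients are told about SSGA, which the article does not state. The severity is should-fix: the primary outcome is not affected, but the data cannot be recovered once patients have answered the item.

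**What to change.** In 2.4.2, replace the item with one arm-neutral question used identically in both groups, for example: *Do you think the acupuncture treatment you are receiving will be effective for your acne?* This makes each patient rate the treatment received and takes the method's name out of the item.

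In 2.5.1, take the scale out of the list compared at weeks 8 and 12, and state that it is compared between groups once, after the first session. Check that the Figure 3 schedule agrees.

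The cost is one questionnaire line, one analysis sentence and a minor notification to the ethics committees. Treatment, sample size and primary outcome do not change. The correction should be made before the first patient completes the scale.

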#### Data collection and management

2.4.3

The data for this study will be collected by the assistant and filled in CPFs. The independent investigator will enter the relevant information and data of this study into an Excel spreadsheet to protect its confidentiality. No one outside the research group will have access to relevant information. Participants’ research information may not be published outside of the research if there is no written permission from the participants.

### Statistical analysis

2.5

#### Clinical data analysis

2.5.1

Statistical analysis of all data will use IBM SPSS statistical version 24.0 software (IBM Corporation, Armonk, New York). For continuous variables, the data will be represented by the mean (standard deviation) or median (interquartile range) according to the normal distribution. Enumerated data will be displayed in percentage. For the primary outcome, we will calculate the IGA score at 8 weeks, and use the χ^2^ test to compare group A and group B. For secondary outcomes, continuous variables including IGA, TCL, Inflammatory lesion count, Non-inflammatory lesion count, Qol-Acne, and the Expectation and Credibility of acupuncture treatment will be compared at 8 and 12 weeks, using an unpaired Student *t* test or Wilcoxon rank-sum test (depending on the situation). A *P* value of <.05 will be considered a limit of statistical significance.

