**Methods::**

The proposed protocol is planned as a randomized, assessor-blind, conventional-treatment-controlled trial to evaluate the efficacy of SSGA on gastrointestinal damp-heat acne. Seventy six gastrointestinal damp-heat acne patients will be randomly divided into 2 groups and receive SSGA or conventional acupuncture treatment. The entire study period is 12 weeks, including an 8-week treatment period and a 4-week follow-up period. All patients will receive 16 sessions of acupuncture treatment over 8 weeks. The primary outcome is the investigation global assessment (IGA) at week 8, which is an overall assessment of the degree of the inflammatory and non-inflammatory lesion. The secondary outcomes include IGA, the total facial lesion count (Total Lesion Count), the acne-specific quality of life, etc at weeks 8 and 12. The Expectation and Credibility of treatment rating scale will be used to measure the patients’ attitudes to acupuncture after the first treatment. Adverse events will also be recorded.

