#### Inclusion criteria

2.2.3

Patients who meet the following conditions will be included:

1.13 to 30 years old, male or female patients with acne.2.Patients meet the diagnostic criteria for acne in Western medicine and the gastrointestinal damp-heat type according to the TCM syndrome differentiation criteria3.Investigation Global Assessment (IGA) score is level 3 (moderate) or level 4 (severe).^[21]^4.Symptoms have been on for more than 6 months.5.Have a certain level of reading comprehension and be able to complete questionnaires independently.6.Patients did not use acne drugs, such as oral, topical, or traditional Chinese medicine, within 4 weeks before entering the group.7.Those who did not participate in other clinical studies within 1 month and were guaranteed not to participate in other clinical studies during this study period.

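### The primary outcome is defined as change in IGA to week 8 but analysed by a χ² test on the week-8 score with no cut-off, and week-8 IGA is tested again as a secondary outcome

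*Protocol article*

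**What the plan says.** The protocol article describes the primary outcome in three places.

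- **Section 2.4.1 (Primary outcome):** "The primary outcome measurement will be expressed by the change in IGA score from baseline to the end of 8-week treatment". The scale "is divided into 6 levels", which are ordered from grade 0 to grade 5.
- **Abstract, Methods:** "The primary outcome is the investigation global assessment (IGA) at week 8", with no mention of change.
- **Section 2.5.1 (Clinical data analysis):** "For the primary outcome, we will calculate the IGA score at 8 weeks", followed by a χ² comparison of group A with group B. Baseline, change, a cut-off and a trend version of the test are not mentioned.

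IGA also appears among the secondary outcomes. Section 2.4.2 states "The secondary measurements will be measured by changes in IGA, total facial lesion counts" and further measures, at weeks 8 and 12 against baseline. Section 2.5.1 then treats IGA as continuous ("For secondary outcomes, continuous variables including IGA, TCL, Inflammatory lesion count") and compares it at both times by unpaired t test or Wilcoxon rank-sum test. The significance limit is P < .05, with sidedness not stated.

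Section 2.5.2 sizes the trial on a further quantity, an effective rate of 76.7% against 98.48%, with a one-sided cut-off. That rate is not defined in terms of IGA.

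**The concern.** A change score and a week-8 score are different variables here, because section 2.2.3 admits patients at grade 3 or grade 4. Grade 2 at week 8 is a fall of one point for one patient and two points for another. The text does not settle which variable decides the trial.

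The test does not fit either variable well. A χ² test on six grades asks whether the two distributions differ in any way, not whether one arm is better. It is weak against the directional shift the trial looks for, and it gives no directional effect estimate. The abstract says the results will feed the sample size of a later trial, and that needs such an estimate.

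Week-8 IGA is also tested a second time, as a continuous secondary outcome. If the two results disagree, the favourable one can be put forward.

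**Working it through.** **1. The plan's own figure.** Section 2.5.2 gives n = π₀(1−π₀){(z_α+z_β)/δ}² with π₀ = 0.767, δ = 0.9848 − 0.767 = 0.2178, z_α = 1.645 and z_β = 1.282. So n = 0.767 × 0.233 × (2.927/0.2178)² = 32.28, stated as about 32. Then 32 × 1.2 = 38.4, stated as 38, and 2 × 38 = 76. The arithmetic reproduces. It concerns a one-sided comparison of rates at 90% power (z_β = 1.282), not a change in IGA and not a six-grade table.

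**2. The χ² test ignores order.** Take an illustrative table with 38 per arm over grades 0–5: 2, 6, 10, 12, 6, 2 against 6, 10, 12, 6, 3, 1. With equal arms, χ² = Σ(a−b)²/(a+b) = 16/8 + 16/16 + 4/22 + 36/18 + 9/9 + 1/3 = 6.52 on 5 degrees of freedom, p = 0.26. Each term belongs to one column, so shuffling the grades leaves the sum unchanged. The Wilcoxon test on the same data gives p = 0.014. The two planned tests of week-8 IGA can therefore disagree.

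**3. Power, by simulation.** The documents give no IGA distribution, so these inputs are assumptions: control distribution at week 8 over grades 0–5 of 5/20/35/25/13/2%; 40% entering at grade 4; baseline effect of 1.5 on the log-odds scale; a common odds ratio for treatment; two-sided 5%.

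| Odds ratio 3 | χ², six grades | χ² on IGA 0–1 | Wilcoxon | Linear model with baseline IGA |
|---|---|---|---|---|
| 38 per arm | 37% | 54% | 67% | 74% |
| 32 per arm | 30% | 46% | 57% | 63% |

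The second row matters because 38 already includes the dropout allowance on 32. With 38 per arm, the six-grade χ², Wilcoxon and adjusted model give about 15/32/37% for an odds ratio of 2 and 60/85/90% for an odds ratio of 4. About 40% of the cells of the six-grade table have an expected count below 5.

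A second set of assumptions (entry grades 50:50, 38 per arm, odds ratio 3) gives 38% for the six-grade χ², 68% for Wilcoxon on the week-8 score and 75% for Wilcoxon on the change. The ordering is the same.

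**4. Two tests of week-8 IGA under the null.** In that second set, the χ² and the Wilcoxon test on the week-8 score each reject in about 5% of trials, and at least one of them rejects in 8.2%. Over the assumptions tried, the figure is about 7–8%.

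**The case against.** The strongest reply is that a responder rate was meant. Section 2.5.2 sizes the trial on rates, section 2.5.1 reports enumerated data as percentages, and χ² suits a 2×2 comparison. On that reading the objection about unordered grades and 5 degrees of freedom falls away. This is plausible, so the six-grade power should not be read as the power of this trial. But no section says which IGA result counts as effective, and sections 2.4.1 and 2.5.1 name a change and a score. On this reading the primary endpoint is undefined, and a cut-off at IGA 0–1 still has less power than the ordinal comparison (54% against 67%).

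Three stronger conclusions are tempting, and the documents do not support them.

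- **That nothing says which of the two week-8 tests decides.** Section 2.5.1 assigns the χ² to the primary outcome and the t test or Wilcoxon to the secondary outcomes. The type I error rises only if that label is set aside, and then to about 7–8%.
- **That ignoring baseline makes the comparison invalid.** Under randomisation an unadjusted week-8 comparison is valid, and the abstract names week-8 IGA as primary. The loss is one of efficiency: 67% to 74% in the illustration, under an assumed baseline effect.
- **That the χ² is a faulty test in itself.** Used alone it holds its level of about 5%. The problem is its fit to the stated outcome.

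It can also be said that the trial aims at feasibility and preliminary efficacy, so power and multiplicity weigh less. That is fair, but it does not remove the conflict between the outcome and its analysis.

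**Conclusion.** The point holds. The primary outcome is a change in section 2.4.1 and a week-8 score in the abstract and section 2.5.1, and the stated χ² has no categories that would make it a test of improvement. Either the test disregards grade order and baseline, or it tests a responder rate that is nowhere defined. Both readings need correction.

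For an odds ratio of 3, the gap between the six-grade χ² and a baseline-adjusted analysis is 74 − 37 = 37 percentage points at 38 per arm and 63 − 30 = 33 at 32 per arm. Against χ² on IGA 0–1 it is 74 − 54 = 20 and 63 − 46 = 17. These sizes rest on the assumed IGA distribution, baseline effect and common odds ratio. The adjusted figure is from a linear model, which corresponds to the ANCOVA option; proportional-odds regression was not itself simulated. The direction is firmer than the sizes.

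Listing week-8 IGA twice is a smaller fault, an opening for selective emphasis. The 90% power implied in section 2.5.2 applies to neither reading of the IGA outcome as now stated.

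**What to change.** 1. State one primary definition in the same words in the abstract and in sections 2.4.1 and 2.5.1.
2. In section 2.5.1, replace the χ² with one prespecified primary analysis: proportional-odds regression of week-8 IGA grade on group, adjusted for baseline IGA grade, or ANCOVA of the change with baseline IGA as covariate. Choose one, and state its sidedness, since section 2.5.2 is one-sided and section 2.5.1 is silent.
3. In sections 2.4.2 and 2.5.1, keep only week-12 IGA as a secondary IGA outcome. Align the abstract's secondary list.
4. If a responder rate is wanted, define it on IGA in advance and list it as secondary.
5. In section 2.5.2, state that the sample size rests on a one-sided comparison of an effective rate that is not the primary endpoint, so its implied 90% power does not carry over to the primary analysis.

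The cost is a text amendment to the abstract and sections 2.4.1, 2.4.2, 2.5.1 and 2.5.2. Baseline IGA is already recorded for eligibility, so no further patients, visits or data are needed, and SPSS fits both models.

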### Study design and ethics

2.1

The proposed study is a prospective, parallel, two-armed randomized controlled trial using a 1:1 allocation ratio with a 4-week follow-up. The study will be conducted at Dongzhimen Hospital of Beijing University of Chinese Medicine and the Third Affiliated Hospital of Henan University of Traditional Chinese Medicine. The outline of the study patient process is in Figure 1.

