#### Randomization and allocation concealment

2.2.6

Patients will be randomly assigned to receive SSGA or conventional acupuncture at a ratio of 1:1. Sealed opaque envelopes will be applied to confirm random hiding. The random sequence number and group assignment information will be sealed in orderly envelopes. With the addition of the patients, these envelopes will be unfolded one by one in order, and the research assistant will record the assigned serial number in the case report form (CRF). The research assistant who does not participate in treatment or evaluation will keep these envelopes.

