## Discussion

3

Acne is a chronic inflammatory skin disease, and its pathogenesis is still not completely clear. Modern studies suggest that its onset is related to the relative increase of androgens, increased secretion of sebum, hair follicles mouth of excessive and Propionibacterium acnes infection and so on. In addition, the immune imbalance, the role of inflammatory factors, and genetic related factors have also been recognized.^[11]^ The general effects of acne are physical sensory symptoms such as skin itching and pain. However, the most serious impact is on the quality of life. This influence is affected by various factors, which makes it difficult to quantitatively analyze. In youth, the self-confidence and self-esteem of acne sufferers are affected. If it can’t be cured, it may bring continuous negative psychological effects on adults, such as shame, embarrassment, depression, anxiety, and even suicide. Therefore, complementary and alternative medicine in modern practice regarding various dermatology is becoming more and more extensive.

As a unique alternative treatment method, acupuncture has the function of “external treatment of internal diseases” and can treat systemic diseases through the conduction of meridians and acupoints.^[25]^ It is widely used in China and has achieved good results in the treatment of acne, chloasma, eczema, allergic skin diseases, and other skin diseases.^[13]^ However, the existing trials only provide routine treatment for this disease and do not conduct syndrome differentiation.^[26–30]^ TCM treats acne and adopts the principle of syndrome differentiation and treatment. Starting from the origin, the advantages are significant.^[31,32]^ Therefore, under the guidance of TCM theory and clinical experience, we have designed a study on acne with the gastrointestinal damp-heat syndrome. This trial is based on the guidance of TCM theory. We aim to evaluate the changes in the count of facial skin lesions and the improvement of quality of life in patients with acne by SSGA. This study is a multi-center clinical randomized trial, which is more in line with clinical practice and closer to the real world. Moreover, the selection of acupoints is within a relatively safe range of the lower limbs, avoiding operations on the local lesions, so the patients’ acceptance is relatively high.

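### Secondary outcomes are defined as changes from baseline, but 2.5.1 fixes unadjusted t or Wilcoxon tests and leaves week value or change open; for lesion counts and Acne-QoL, adjusting for baseline and hospital is clearer and usually more precise

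*Protocol article*

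**What the plan says.** Protocol article, section 2.4.2 (Secondary outcome measurements), sets the outcome scale: "The secondary measurements will be measured by changes in IGA, total facial lesion counts", then the inflammatory and non-inflammatory counts and Acne-QoL, "at 8 and 12 weeks compared with baseline display".

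Section 2.5.1 (Clinical data analysis) sets the test. IGA, the three lesion counts, Acne-QoL and the Expectation and Credibility scale "will be compared at 8 and 12 weeks, using an unpaired Student" t test or a Wilcoxon rank-sum test, depending on the situation. No baseline covariate and no hospital term is named. The criterion is that a P "value of <.05 will be considered a limit of statistical significance"; sidedness is not given.

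Two hospitals recruit (section 2.1, and section 3: "This study is a multi-center clinical randomized trial"). Section 2.5.2 gives a total of 76 patients, 38 per group.

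**The concern.** Sections 2.4.2 and 2.5.1 do not fix one analysis. Read alone, 2.5.1 could mean a comparison of the values recorded at weeks 8 and 12. Read with 2.4.2, it could mean a comparison of changes. The two have different precision and can give different answers in the same data, so the choice stays open until the data are seen.

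On either reading the named tests make less use of the baseline value than they could. That value must be recorded for the change in 2.4.2 to exist, and the hospital is known for every patient. What is at stake is precision in the lesion counts and quality of life, which section 3 describes as the trial's aim. The abstract adds that the results will feed the sample size of later, larger studies, so a precise estimate with an interval has direct use.

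**Working it through.** **The plan's own figure.** Section 2.5.2: 0.767 × 0.233 × (2.927 / 0.2178)² = 32.28, stated as 32; 32 × 1.2 = 38.4, stated as 38; two groups make 76. It reproduces. It concerns the effective rate and enters here only as 38 per arm.

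**Inputs.**
- 38 per arm, N = 76 (section 2.5.2).
- Two hospitals, so one hospital term (section 2.1).
- Correlation ρ between baseline and follow-up: not in the documents, so assumed and varied.
- Equal SD at baseline and follow-up: assumed.
- No hospital effect in the table: assumed.

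**Formulas.** Variance of the group difference, relative to an unadjusted test of the week value:
- week value: 1
- change score: 2(1 − ρ)
- ANCOVA on baseline and hospital: (1 − ρ²) × (N − 3)/(N − 5) = (1 − ρ²) × 73/71, where 73/71 = 1.028 is the price of estimating two covariate terms.

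| ρ (assumed) | Week value | Change score | ANCOVA | ANCOVA against week value | ANCOVA against change score |
|---|---|---|---|---|---|
| 0 | 1 | 2.00 | 1.028 | 2.8% higher | 48.6% lower |
| 0.2 | 1 | 1.60 | 0.987 | 1.3% lower | 38.3% lower |
| 0.3 | 1 | 1.40 | 0.936 | 6.4% lower | 33.2% lower |
| 0.5 | 1 | 1.00 | 0.771 | 22.9% lower | 22.9% lower |
| 0.7 | 1 | 0.60 | 0.524 | 47.6% lower | 12.6% lower |

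**Break-even against the week-value test.** (1 − ρ²) × 73/71 = 1 gives ρ² = 2/73 = 0.027, so ρ is about 0.17. Below that ANCOVA loses, by at most 2.8% in variance at ρ = 0. Against the change score it had the lower variance at every ρ computed, from 0 to 0.8.

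**In terms of power.** For an assumed difference of 0.65 SD, two-sided 0.05 (sidedness assumed) and 38 per arm, power for week value / change / ANCOVA is:
- ρ = 0.3: 81% / 67% / 83%
- ρ = 0.5: 81% / 81% / 90%
- ρ = 0.7: 81% / 96% / 98%

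**Simulation check**, 4,000 trials per setting with 38 per arm. Type I error was 4.1% to 5.4% across all three analyses. At ρ = 0.5 without a hospital effect the empirical standard errors were 0.232, 0.231 and 0.204. Then (0.204 / 0.232)² = 0.773, against 0.771 from the formula.

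**Why ANCOVA removes the ambiguity.** Let Y be the week value, B the baseline and G the group. The model Y − B = a + τG + βB + hospital is the same as Y = a + τG + (β + 1)B + hospital. The group effect τ is identical; only the slope on baseline moves by 1.

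**The case against.** The strongest reply is that the planned tests are sound. Under randomisation an unpaired t or Wilcoxon test holds its error rate, and its p-value already allows for chance imbalance. That stands: a reader might infer that the planned comparisons are biased or invalid, and neither the documents nor the simulation supports it. What remains is a matter of efficiency and clarity in secondary outcomes of a trial described as assessing feasibility and preliminary efficacy.

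A second reply concerns the wording. A reader might infer that 2.5.1 tests raw values and so contradicts 2.4.2 outright. The text does not go that far: a test of change scores is a natural joint reading. The defect is that the tested quantity is unstated. The variance comparison is therefore given against both readings.

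Third, the size of the gain rests on correlations that the documents do not give. This also stands. At ρ = 0.2 the gain over a week-value test is about 1%, and over a change-score test at ρ = 0.7 it is about 13%. Nor do the documents show that lesion counts or quality of life vary widely at entry, so the point does not rest on that.

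Fourth, a reader might take the envelopes, of which section 2.2.6 says "these envelopes will be unfolded one by one in order", to show that allocation is unstratified and that the hospitals will be unbalanced. The article does not say whether blocks or strata are used, and a condensed article may leave that to the full protocol. No criticism of the randomisation follows.

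Finally, a separate analysis plan may exist and may add detail. But section 2.5.1 does name a test, and it is this stated choice that can be improved.

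**Conclusion.** The point holds as one of precision and clear specification. For outcomes defined as changes from baseline, section 2.5.1 fixes unadjusted tests and leaves the tested quantity open. With 38 per arm and an assumed correlation of 0.3 to 0.7, adjustment for baseline and hospital lowers the variance by about 6% to 48% against a week-value test and by about 33% to 13% against a change-score test. The possible loss against the week-value test is at most about 3%, and only below a correlation of about 0.17. These figures assume equal SDs at baseline and follow-up and no hospital effect.

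The scope is limited. The gain is probably smallest for IGA, because section 2.2.3 admits only grades 3 and 4 and the baseline therefore takes two values. The point does not apply to the Expectation and Credibility scale, which is taken after the first treatment and has no described baseline. The sample size is unaffected.

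**What to change.** In section 2.5.1, for total, inflammatory and non-inflammatory lesion counts and Acne-QoL, replace the unpaired t or Wilcoxon test by ANCOVA at weeks 8 and 12, or by one mixed model over both weeks, with group, the baseline value of that outcome and hospital as terms. If the counts are skewed, analyse them on the log scale or with a negative binomial model, and fix that choice before the allocation is revealed. Report the adjusted difference with its 95% CI, or the adjusted ratio for log-transformed or negative binomial counts. Leave the Expectation and Credibility scale out of the baseline adjustment.

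The cost is a few lines of wording and slightly more analysis work. No new data, visits or patients are needed. The one statistical price is a trivial loss of precision if the correlation turns out to be very low.
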